#### Recruitment and Eligibility Criteria

Participants will be recruited from multiple NHS hospital sites across North West England and North Wales using the National Institute for Health Research (NIHR) Clinical Research Network (CRN) research nurses (RNs). Patients will be eligible to take part if they meet the following inclusion criteria: (a) have been diagnosed with cancer of any type in the past six months, (b) received anticancer treatment with curative intent, (c) are aged 16 years or older, (d) are sufficiently proficient in English to provide informed consent and use the program; and (e) able to access the internet and have (or be willing to set up) an email address. Patients will be ineligible or excluded if they have a severe comorbidity considered to interfere with the individual’s ability to complete the requirements of the study or to provide informed consent (eg, intellectual disability or neurological impairment). Nurses will complete fortnightly screening logs to provide anonymized information on the number of patients screened, eligible, and then provided with a trial information pack to inform later potential implementation decisions.

CRN RNs will screen regular multidisciplinary team meeting records for eligible patients and identify when their next clinical appointment will be. The CRN RN will approach each patient face-to-face to tell them about the study and provide an information pack. Where no appointment is planned within the subsequent 6 weeks, or where face-to-face introduction would be otherwise problematic (eg, lack of private space to discuss the study), our protocol permits a telephone introduction to the study. At the start of recruitment, records of existing multidisciplinary team meetings will be retrospectively searched for any patients meeting the eligibility criteria, although we anticipate that the majority of our sample will be recruited through prospective recruitment over a 12-month recruitment period.

Assuming a conservative 40% consent rate [27], we estimate that 735 patients will need to be approached to reach our target sample size. We will recruit a range of cancer teams to ensure clinical diagnostic and demographic variability.

### Procedure

After reading information provided by the CRN RNs, patients wishing to take part in the study can access our study recruitment website via a link in their information pack. This provides a full trial information sheet and access to a web-based consent form. Once their consent is submitted, participants are redirected immediately to the baseline survey via the *Qualtrics survey platform* (Qualtrics). Participants also will receive an automated email with a link to complete the baseline questionnaire at a later date or in a number of sittings if they prefer*.* Upon full completion of the baseline questionnaire, an unblinded member of the research team will complete the study arm allocation using a computerized randomization allocation system using *REDCap* software (Vanderbilt University) [36]. The randomization algorithm was set up to ensure equal numbers of participants in both the intervention and control arms, stratified by cancer diagnosis to ensure the spread of patients across both trial arms. The randomization system was set up and is overseen by the Liverpool Clinical Trials Centre. Following allocation, participants are either emailed account details to access the FMW UK website (intervention group) or sent a PDF copy of a site-specific information pack listing existing local and national sources of psychosocial support that they can access as part of treatment as usual (control group; Figure 1). Control participants also have the option to receive a hard copy of the information pack via the post.

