### Participants

#### Sample Size Calculation

Calculations were based on the primary outcome of change in cancer-specific distress between the two patient groups. The original FMW RCT sample size calculation [27] used a standardized effect size of 0.35 and an SD of 4 units, which equates to an absolute change in cancer distress scores of 1.4 units. This study observed a larger than expected SD and we propose a sample size based on a conservative estimate of the residual SD of 7 units accordingly (but keeping the clinically relevant difference at the aforementioned 1.4 units). The correlation between successive measurements on the same patient is assumed to be high, and so a conservative *r*=0.70 was used. Sample size calculations were performed assuming a paired two-tailed *t* test using the derived SD of the change in the primary outcome of 5.42. Assuming a patient attrition of 20% and α of .05, 294 patients (147 per study arm) are required for a statistical power of 80% [35]. We will allow up to 30% overrecruitment to mitigate the effects of missing data and to allow for at least minimal recruitment of less common cancer types.

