### Analysis

The analysis plan matches the Australian FMW RCT [27] as closely as possible. Members of the research team involved in the analysis will be blinded to the condition allocation until the end of the trial. First, we will conduct data cleaning to ensure that all data values are possible and plausible. Errant data entries will be deleted from the final analysis data set and missing data will be handled using either prorating or imputation methods as is (1) appropriate to the collected data and (2) congruent with the specific scoring instructions for the psychometric measure from which there is a missing response.

Descriptive statistics will be used to provide sample characteristic information and to identify any potentially prognostic demographic or clinical covariates. Inferential statistical analyses are powered to undertake mixed model repeated measures analyses to examine intervention effects on change from baseline to follow-up for each outcome, using intention-to-treat analysis. Two models will be run for each: (1) unadjusted, accounting for covariance of baseline measures of outcomes and (2) fully adjusted, controlling for all potential confounding variables assessed. Where possible and adequately powered, we will include potential confounders in our analyses and evaluate the effects of missing data using sensitivity analysis. Cohen *d* effect sizes reflect intervention effects, and clinically significant changes will be assessed using reliable change indices. The health care use outcome will be summarized descriptively for activity counts and cumulative costs estimated by assigning unit costs to units of activity. Cost summaries are derived from discrete payer perspectives. Generalized linear models will be used to adjust for the same confounding variables as in the efficacy analysis. All quantitative data analyses will be undertaken in R software (R Foundation for Statistical Computing) [50] where possible, with any supplementary analyses conducted in IBM SPSS as appropriate*.*

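### Cancer diagnosis stratifies the randomisation, but model 1 omits it and model 2 does not commit to it; naming it as a covariate is a free improvement

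*Protocol article*

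**What the plan says.** Protocol article, Procedure: the allocation algorithm aims at equal numbers in the two arms and is "stratified by cancer diagnosis to ensure the spread of patients across both trial arms". The number of strata, their definition and the block structure are not given.

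Protocol article, Analysis: two mixed models are planned for each outcome.

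- The first is "unadjusted, accounting for covariance of baseline measures of outcomes". Its only stated covariate is the baseline outcome.
- The second is "2) fully adjusted, controlling for all potential confounding variables assessed".

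A further sentence makes adjustment conditional: "Where possible and adequately powered, we will include potential confounders in our analyses". The cost models are to adjust for the same confounders as the efficacy analysis. No model is designated primary, and the stratification factor is not named as a term in any of them.

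**The concern.** Stratified allocation keeps the arms similar in their mix of diagnoses. If diagnosis is related to outcome, the treatment estimate then carries little or no between-diagnosis variance. A model without the strata still counts that variance as error, so its reported standard error is larger than the true one. The confidence interval is wider than it need be and some power is lost.

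Model 2 does not clearly repair this. It is framed around confounding, whereas a stratification factor belongs in the model because of the design, whether or not the arms look imbalanced on it. Its adjustment is also conditional on feasibility and power. Cancer type is not named among the self-reported characteristics (Study Outcomes) or the items extracted from hospital records (Procedure). Those extraction items may not be a complete list, so it is unclear whether the variables assessed include it.

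**Working it through.** **Inputs from Sample Size Calculation.** The difference is 1.4 units ("keeping the clinically relevant difference at the aforementioned 1.4 units"), the SD is 7 ("a conservative estimate of the residual SD of 7 units") and the correlation is 0.70 ("a conservative *r*=0.70 was used"). Alpha is 0.05 two-sided, attrition 20%, and the sample 147 per arm.

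**Reproducing the plan's figure.** SD of change = 7 × √(2 × (1 − 0.70)) = 5.42, as stated. With the paired formula that the article names, n = ((1.960 + 0.842) × 5.42 / 1.4)² = 117.6, and 117.6 / 0.8 = 147. A two-sample comparison of change on the same inputs needs 236 completers per arm (295 with attrition). That is a separate matter. It is noted here only because it sets the power from which any loss is measured, so three starting points are shown below.

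**Assumed input.** R² is the share of residual variance, after baseline adjustment, that diagnosis explains. The article gives no value; 0 to 0.10 is taken as the range.

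**Formulas**, for one follow-up visit, with total residual variance fixed and allocation balanced within strata:

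- Reported SE / true SE without strata = 1/√(1 − R²)
- Type I error without strata = 2 × (1 − Φ(1.96/√(1 − R²)))
- Power without strata = Φ((λ − 1.96)/√(1 − R²))
- Power with strata = Φ(λ/√(1 − R²) − 1.96)

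Here λ is the difference divided by its SE when R² = 0:

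- A, the article's nominal 80% power: λ = 1.960 + 0.842 = 2.802.
- B, two-sample change score, 118 completers per arm: λ = 1.4 / (5.42 × √(2/118)) = 1.984.
- C, baseline-adjusted, SD = 7 × √(1 − 0.49) = 5.00, 118 per arm: λ = 1.4 / (5.00 × √(2/118)) = 2.151.

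**Worked case, C with R² = 0.10.** √0.90 = 0.9487. SE ratio = 1/0.9487 = 1.054. Type I error = 2 × (1 − Φ(2.066)) = 0.039. Power without strata = Φ(0.191/0.9487) = 58.0%; with strata = Φ(2.151/0.9487 − 1.96) = Φ(0.307) = 62.1%.

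| R² | SE ratio | Type I error, strata omitted | A: without / with | B: without / with | C: without / with |
|---|---|---|---|---|---|
| 0 | 1.000 | 0.050 | 80.0 / 80.0% | 51.0 / 51.0% | 57.6 / 57.6% |
| 0.02 | 1.010 | 0.048 | 80.2 / 80.8% | 51.0 / 51.8% | 57.7 / 58.4% |
| 0.05 | 1.026 | 0.044 | 80.6 / 82.0% | 51.0 / 53.0% | 57.8 / 59.8% |
| 0.10 | 1.054 | 0.039 | 81.2 / 84.0% | 51.0 / 55.2% | 58.0 / 62.1% |

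**Simulation check** (six assumed strata, blocks of 4, 236 completers in total, SD 5.42, 4,000 runs per setting). At R² = 0.10 the model without strata reported a mean SE of 0.705 against an empirical SE of 0.67 to 0.68. Its type I error was 4.3%, against 5.4% with strata (Monte Carlo error about 0.3 points). Power was 51% without strata and 55% with them. At R² = 0 the two models agreed: power 50.5% and 50.4%, mean SE 0.706 in both.

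**The case against.** The article is condensed; a fuller protocol is said to be held elsewhere and the SAP is not shown. Exact covariate lists usually sit there, and reporting an unadjusted model beside an adjusted one is no error in itself. That stands as far as model 2 goes. It does not fully answer the point, because the article does state what model 1 contains, and that leaves out the factor built into the randomisation.

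Three stronger readings are tempting, and the article does not support them.

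- A reader might infer that model 1 certainly loses power. It does so only if diagnosis is prognostic beyond the baseline score. No figure is given, and the loss can be zero.
- A reader might infer that the plan expects outcomes to differ between cancer groups. It does not say so. The stated purpose of stratifying is the spread of patients, and recruiting a range of cancer teams is for diagnostic and demographic variability. The Background even reports that psychological variables predict distress-related outcomes independently of clinical characteristics.
- A reader might infer that model 2 is simply selected from the data and so excludes diagnosis. Its wording covers all potential confounders assessed, which could include diagnosis. The nearby conditions make this ambiguous, not excluded.

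The calculation also assumes balance within strata. All cancer types are eligible and 20% attrition is expected, so sparse strata may weaken that balance. The standard error of model 1 would then be less overstated, but the argument for including the stratum would remain.

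**Conclusion.** The point holds in a limited, conditional form. Model 1 omits the randomisation stratum, model 2 does not commit to it, and no model is primary. Any error is on the conservative side: no bias in the treatment effect and no excess of false positives. Over an assumed R² of 0 to 0.10, the loss of power is 0 to about 3 points from the nominal 80%, and 0 to about 4 points from the two-sample starting points. These figures rest on the assumed R², balance within strata and a single-visit approximation to the mixed model. The low starting power in B and C comes from the sample-size formula and should not be charged to this point. I class it as a free improvement, not a flaw that threatens the trial's conclusions.

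**What to change.** Before unblinding, state in the analysis plan that cancer diagnosis, as coded in the randomisation system, enters model 1 as a fixed effect, and also whichever model is designated primary. Fix in the same place a rule for pooling rare diagnoses, since eligibility covers every cancer type and some strata will be small. Carry the term into the cost models, which already share the efficacy adjustment variables.

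The cost is one or two sentences and a few degrees of freedom. The variable is already held for randomisation, and if diagnosis turns out not to be prognostic the results barely change. The change also removes a discretionary covariate choice.

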**Figure 1 figure1:**
[figure not shown]
Procedure for the Finding My Way UK Clinical Trial. CRN: Clinical Research Network; FMW: Finding My Way; NIHR: National Institute for Health Research.

Those given immediate access to FMW UK are encouraged to log in within one week, study the instruction materials provided, and select the order in which they would like to receive access to the intervention modules (if no preference is given, participants receive in default numerical order). A reminder (text or phone, as preferred) is then sent if they have not logged in during this time. Modules are then automatically released once per week; access to the booster module is also released one month after completion of the main program. Regular automated email reminders are sent as new modules are released each week.

At the point of being informed of intervention allocation, automated email reminders to complete the study questionnaires are set up through *Qualtrics*. Text messages or phone call reminders (as preferred) are sent for a period of 7 days without submission of any specific questionnaire. Questionnaires are completed at the end of the third (midintervention) and sixth (posttreatment) week, and then at 3- and 6-month follow-ups, both timed from the release of the posttreatment questionnaire. Participants are sent a debrief sheet at this point, and control arm participants are granted access to the FMW UK website. At this point, CRN RNs complete clinical data extraction from hospital records using a standard form; this includes information about the date of diagnosis, primary or recurrent diagnosis, curative or palliative treatment intent, principle treatment approach adopted (surgery, chemotherapy, radiotherapy, or watch-and-wait), date of the end of active treatment (if applicable), date of any recurrence or relapse (if applicable), date of death (if applicable), known referrals to mental health care teams since diagnosis, number of days of inpatient care since study enrollment and types of health care professionals seen during these stays, the number of outpatient visits since study enrollment and types of health care professionals seen during these visits, and any diagnostic tests conducted since study enrollment. As this study is registered on the UK NIHR CRN Portfolio, costs for most CRN RN activities (both recruitment and clinical data collection) are covered by CRN Study Support Services, with costs for additional archiving at each site reimbursed by the clinical trial research grant.

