##### The UK Cancer Costs Questionnaire

The UK Cancer Costs Questionnaire [42] is a flexible modular self-report measure of resource use by people with cancer and those with a previous diagnosis of cancer. The UK Cancer Costs Questionnaire assesses employment status, family support provided, government benefits received, and support provided by other organizations over the previous 3 months. The UK Cancer Costs Questionnaire prioritizes brevity to minimize the burden of data collection for participants. For full health care use outcome data, this self-report questionnaire is supplemented by health service resource use data extracted from clinical records and the calculation of Quality-Adjusted Life Years from the QLQ-C30.

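### Mental health referrals are extracted from diagnosis but the other record-based use items from enrolment, so 0% to 45% of the referral window precedes randomisation

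*Protocol article*

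**What the plan says.** The Procedure section of the protocol article (text after Figure 1) lists what research nurses extract from hospital records, once, at the end of follow-up. One sentence gives two starting points: "known referrals to mental health care teams since diagnosis, number of days of inpatient care since study enrollment". The remaining use items follow the enrolment rule: "the number of outpatient visits since study enrollment" and "any diagnostic tests conducted since study enrollment". No reason is given for the different start for referrals.

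Three other places bear on the point:

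- **Eligibility** (Recruitment and Eligibility Criteria): patients must "have been diagnosed with cancer of any type in the past six months".
- **Role of record data** (The UK Cancer Costs Questionnaire): the self-report measure is "supplemented by health service resource use data extracted from clinical records".
- **Analysis**: "The health care use outcome will be summarized descriptively for activity counts and cumulative costs estimated by assigning unit costs to units of activity". Generalized linear models then adjust for the same confounders as the efficacy analysis.

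The Discussion (Trial Status) names reduced need for broader health care use among the things the trial will test.

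**The concern.** A referral made before allocation cannot have been affected by the programme. A window that opens at diagnosis mixes such referrals with later ones that the programme might change. As described, the item is clean for neither natural use:

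- **As a measure of use after randomisation**, it includes earlier referrals and covers a longer period than the items it would be added to.
- **As a baseline characteristic or covariate**, it includes referrals made after allocation, because it is collected only once, at the end of follow-up.

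Referral to a mental health team is close to what a psychological intervention might plausibly change, so the record is worth having in usable form.

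**Working it through.** The article states no figure for the share of the window before randomisation, so there is none to reproduce. The check rests on these inputs.

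**Inputs**

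- Diagnosis to entry: 0 to 6 months, taken as 0 to 26 weeks (eligibility criteria). No mean or distribution is given.
- Allocation to posttreatment: 6 weeks (Procedure: "Questionnaires are completed at the end of the third (midintervention) and sixth (posttreatment) week").
- Posttreatment to last follow-up: 6 months, taken as 26 weeks (Procedure: "then at 3- and 6-month follow-ups, both timed from the release of the posttreatment questionnaire").
- Post-allocation window: 6 + 26 = 32 weeks, approximately. The short gap between consent and allocation, while the baseline questionnaire is completed, is ignored.

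**Step 1. Share of the window before entry** = p / (p + 32), where p is the lag in weeks.

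| Lag p | Share |
|---|---|
| 0 weeks | 0% |
| 13 weeks | 13/45 = 28.9% |
| 26 weeks (maximum) | 26/58 = 44.8% |

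The 0% to 45% range follows from the documents. The 29% figure needs an assumed mean lag of 13 weeks, such as entry spread evenly over six months. It is then the share of total person-time; the average of the individual patients' shares under that spread is 27%. These are shares of time. They equal shares of referrals only if the referral rate is constant.

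**Step 2. Effect on a ratio, if arms are compared.** With a constant rate and a true post-randomisation rate ratio RR, the ratio seen is (p + 32 × RR) / (p + 32). RR = 0.70 is illustrative.

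- p = 13: (13 + 22.4) / 45 = 0.787
- p = 26: (26 + 22.4) / 58 = 0.834

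The distortion is modest at short lags. It stays within 10% of the truth, that is at or below 0.77, while (p + 22.4) / (p + 32) ≤ 0.77. This gives p ≤ 2.24 / 0.23 = 9.7 weeks.

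**Step 3. Effect on a difference.** Randomisation balances earlier referrals in expectation, so they cancel from the expected absolute difference, which is unbiased. They do add noise. If the variance of a count is proportional to window length at a constant rate equal in both arms, the standard error of the difference is multiplied by √((p + 32) / 32).

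- p = 13: √(45/32) = 1.19, an increase of about 19%
- p = 26: √(58/32) = 1.35, an increase of about 35%

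**Step 4. With a window from randomisation.** The pre-randomisation share is zero, and 0.70 is seen as 0.70.

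**The case against.** A reader might infer that the plan compares referrals between arms and that this comparison is diluted. The article does not support so firm a statement. Referrals are not listed among the primary or secondary outcomes. The costs questionnaire section and the Analysis section refer to record-based resource use and units of activity without naming referrals, and nothing says that a referral is costed. In the extraction list the item sits between clinical history and use counts, and unlike inpatient days and outpatient visits it is not worded as a number. It could be meant as a clinical descriptor. All of this stands, and it makes the dilution conditional.

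A reader might also infer that referrals cannot be separated afterwards. The article lists dates for diagnosis, end of treatment, recurrence and death but none for referrals. It is, however, a summary; the extraction form and full protocol are not shown, and the form may date each referral.

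Two further points stand. Outpatient and inpatient contacts are recorded from enrolment with the type of professional seen, so some mental health contact after entry is already captured on the right window. And the absolute difference is not biased.

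The objection does not remove the mismatch itself. The starting point for referrals is a stated rule, not a detail left to another document. Reading the item as a descriptor or covariate does not rescue it either, because it is collected after follow-up and includes post-randomisation events.

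**Conclusion.** The point holds as a minor one. Referrals are the only record-based use item not counted from enrolment, and between 0% and 45% of their window precedes randomisation. The 29% figure depends on an assumed 13-week mean lag.

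If referrals enter the health care use counts or costs, then at a constant rate a true ratio of 0.70 would appear as 0.79 to 0.83 for lags of 13 to 26 weeks. The standard error of the difference would rise by about 19% to 35% over the same range, with no bias in the expected absolute difference. The lag distribution, the constant rate and the 0.70 are assumptions; the article gives none of them.

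At most one component of a secondary outcome is affected. The primary outcome is untouched unless the item is entered in the fully adjusted model. That model is described as controlling for all potential confounders assessed, but referrals are not named as one. If the item were entered, the model would condition on something the intervention may have changed.

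**What to change.** On the extraction form, record a date for each mental health referral, or replace the single item with two fields: diagnosis to randomisation, and randomisation to the 6-month follow-up. Use only post-randomisation referrals in any use counts and costs, so that they share a window with inpatient days, outpatient visits and tests. Use only pre-randomisation referrals as a baseline descriptor or covariate. State which role the item has. If the form already dates referrals, it is enough to say that they will be split at randomisation.

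The cost is one changed line on a form that nurses already complete from the same records, with no extra visit or participant. The downside is slightly more data entry and a smaller post-randomisation count.
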